## Abstract

**Background:**

Patients with gastric cancer experience different degrees of fear of cancer recurrence. The fear of cancer recurrence can cause and worsen many physical and psychological problems. We considered the “intimacy and relationship processes in couples’ psychosocial adaptation” model.

**Objective:**

The study aims to examine the effectiveness of a marital self-disclosure intervention for improving the level of fear of cancer recurrence and the dyadic coping ability among gastric cancer survivors and their spouses.

**Methods:**

This is a quasiexperimental study with a nonequivalent (pretest-posttest) control group design. The study will be conducted at 2 tertiary hospitals in Taizhou City, Jiangsu Province, China. A total of 42 patients with gastric cancer undergoing chemotherapy and their spouses will be recruited from each hospital. Participants from Jingjiang People’s Hospital will be assigned to an experimental group, while participants from Taizhou People’s Hospital will be assigned to a control group. The participants in the experimental group will be involved in 4 phases of the marital self-disclosure (different topics, face-to-face) intervention. Patients will be evaluated at baseline after a diagnosis of gastric cancer and reassessed 2 to 4 months after baseline. The primary outcome is the score of the Fear of Progression Questionnaire-Short Form (FoP-Q-SF) for patients. The secondary outcomes are the scores of the FoP-Q-SF for partners and the Dyadic Coping Inventory.

**Results:**

Research activities began in October 2022. Participant enrollment and data collection began in February 2023 and are expected to be completed in 12 months. The primary results of this study are anticipated to be announced in June 2024.

**Conclusions:**

This study aims to assess a marital self-disclosure intervention for improving the fear of cancer recurrence in Chinese patients with gastric cancer and their spouses. The study is likely to yield desirable positive outcomes as marital self-disclosure is formulated based on evidence and inputs obtained through stakeholder interviews and expert consultation. The study process will be carried out by nurses who have received psychological training, and the quality of the intervention will be strictly controlled.

**Trial Registration:**

ClinicalTrials.gov NCT05606549; https://clinicaltrials.gov/study/NCT05606549

**International Registered Report Identifier (IRRID):**

DERR1-10.2196/55102

## Introduction

In 2020, there were 1,089,103 new cases of gastric cancer and 768,793 deaths worldwide, accounting for 5.6% and 7.7% of the total incidences and deaths, respectively [1]. The standardized morbidity and mortality rates were 11.1/100,000 and 7.7/100,000, respectively, and the cumulative morbidity and mortality risks of those aged 0 to 74 years were 1.31% and 0.90%, respectively. Gastric cancer ranks second in terms of cancer incidence and mortality in China, with 679,000 cases and 498,000 deaths, followed by lung cancer (733,000 deaths) [2]. The disability-adjusted life years associated with gastric cancer in China is 9.825 million person-years, accounting for 44.21% of the gastric cancer cases globally [3].

Advancements in postoperative chemotherapy for gastric cancer have led to an increase in the 5-year survival rate of patients to 68% [4]. Although surgery and combined chemotherapy have improved the survival of patients to a certain extent, the high postoperative recurrence rate and metastatic rate, as adverse psychological events, have a tremendous psychological burden on patients [4]. The fear of cancer recurrence, which first appeared in the subject of oncologic psychology, has particular specificity and independence, which is different from other mental and psychological diseases [5]. Studies reported that about 72% of patients experienced various degrees of fear of cancer recurrence during cancer, of which about 46% were mild or moderate and about 7% were severe [6]. To our knowledge, to date, there have been no psychological intervention studies explicitly targeting the fear of cancer recurrence in Chinese patients with gastric cancer, and only 1 study has conducted a cross-sectional survey of cancer recurrence fear in patients with gastric cancer, which ignored the effect on spouses [7]. However, a spouse’s high fear of cancer recurrence can affect the spouse’s physical and mental health and further jeopardize the patient’s health [8]. Therefore, designing a brief, practical, and feasible intervention to alleviate the fear of cancer recurrence in Chinese patients with gastric cancer and their spouses is critical.

Researchers, patients with cancer, representatives of patient rights, policymakers, and oncology psychologists from many countries reached an expert consensus, which defined the fear of cancer recurrence as “fears and concerns of patients with cancer regarding possible future cancer recurrence and/or metastasis and/or progression” [9]. The primary manifestations of high-level fear of cancer recurrence have been explained as follows: “highly focused, highly concerned, persistent, hypervigilant of physical symptoms and present for at least 3 months” [10].

The treatment cycle of advanced gastric cancer is long, and the recurrence rate is high. Although the progress of medical technology and the resection rate of advanced gastric cancer have increased, the high postoperative recurrence rate and metastatic rate, as adverse life events, have a tremendous psychological impact on patients [11]. Adverse reactions, such as nausea, vomiting, dry mouth, constipation, and bone marrow suppression, aggravate the psychological burden of patients, making them more fearful of the recurrence and progression of the disease [12].

Several studies [12-14] showed that the level of fear of cancer recurrence (as measured by the Fear of Progression Questionnaire-Short Form [FoP-Q-SF]) among patients with gastric cancer (120-170 cases) was middle to high (score of 35.43-42.3 points), the physical health dimension score was 18.09 (SD 4.52), and the social family dimension score was 17.34 (SD 6.34). The scores of the fear of cancer recurrence were higher in patients with gastric cancer than in patients with breast cancer [15] and early-stage prostate cancer [16]. A previous study [17] found that Chinese patients with gastric cancer have less knowledge of the fear of cancer recurrence. High levels of fear of cancer recurrence seriously affect the health of patients with gastric cancer, resulting in a series of dysfunctional behaviors, including avoidance behavior, hypervigilance of symptoms, and inability to plan for the future, which can reduce quality of life, and at the same time, the unmet supportive needs of cancer patients can lead to lower treatment compliance. These effects can persist for months or even years after treatment, and in severe cases, they can lead to anxiety disorders, posttraumatic stress symptoms, and depression [18].

In the relationship intimacy model of couples’ adaptation to cancer by Manne et al [19], the authors emphasized that self-disclosure in relationship-enhancing behaviors is the primary factor affecting the psychological adjustment of cancer patients and their spouses and plays a positive role in the face of cancer. Marriage psychoeducation can help couples understand the value of communicating with each other, provide emotional and problem-focused support, help in the takeover of a spouse’s responsibilities and tasks when one spouse is stressed, and help couples work together to cope when both partners are stressed [20]. In the long run, improvements in dyadic coping are more likely to increase relationship satisfaction than improvements in communication skills [21]. In short, dyadic coping is strongly associated with relationship satisfaction. Therefore, incorporating dyadic coping into a relationship enhancement program may benefit couples’ relationships [22].

Emotional disclosure is a core component of marital emotional support, and it involves expressing feelings, ideas, and opinions to each other [23]. Couple discussion of cancer-related distress may help spouses understand the needs of patients and provide more effective support. Married patients with cancer tend to rate their spouses as their most important confidant. However, patients with cancer often feel constrained in talking about their concerns with their spouses, and partners often withdraw or distance themselves from the emotional distress of patients [24]. These avoidance patterns are present even in couples with satisfying relationships. The inability of patients to talk openly with their spouses about their cancer-related concerns may reduce the ability of couples to cope with stress and compromise the quality of the patient-partner relationship and the patient’s psychological adjustment.

Multiple linear regression analysis results showed that the self-disclosure and intimacy of patients influenced their fear of cancer recurrence [8]. To date, most intervention studies focused on the impact of self-disclosure on the psychological aspect of patients, and they ignored the role of their spouses regarding the psychological state [25-27] and failed to treat patients and their spouses as a whole [12]. Given the vast differences between Western countries and China in terms of race; cultural background; religious beliefs; economic development; and the adaptability and accuracy of the related theory, evaluation scale, and influencing factor analysis, the study results based on Western cultural background cannot be directly applied to the Chinese population. Research on spousal disease communication has primarily focused on patients recovering from breast cancer, lung cancer, and even prostate cancer [28,29]. The treatment cycle for advanced gastric cancer is extended, and the recurrence rate is high, which can intensify the psychological burden on patients [12]. During chemotherapy, patients with gastric cancer encounter numerous dietary restrictions and potential complications, such as nausea and vomiting, heartburn, and acid reflux, resulting in a loss of appetite for food [30]. In Chinese culture, it is believed that food is of utmost importance to people. Being unable to eat or having no appetite is a sign of worsening disease, which further exacerbates both the psychological and physical burdens of patients. No research has been performed on the spousal communication of patients with gastric cancer. Additionally, the research findings of other types of cancers cannot be generalized to patients with gastric cancer, and it is necessary to implement targeted psychological intervention measures for Chinese patients with gastric cancer.

The main objective of this study is to assess a marital self-disclosure intervention that is suitable and feasible based on Chinese culture and clinical practice, focuses on the fear of cancer recurrence, guides patients to adjust to a positive attitude through couple self-disclosure, and improves cancer recurrence fear and the marital relationship with their spouses. If the intervention is proven to be effective, the intervention can be adopted as a practical strategy of psychological care for patients with gastric cancer in China.

## Methods

### Aim

This study aims to develop a marital self-disclosure intervention and evaluate the effectiveness of this intervention for improving the fear of cancer recurrence and the dyadic coping ability in Chinese patients with gastric cancer and their spouses. The trial was registered in November 2022 at ClinicalTrials.gov (NCT05606549).

### Hypotheses

The main hypothesis is as follows: Compared with the control group, participants (patients with gastric cancer and their spouses) in the experimental group show lower scores on the FoP-Q-SF after the intervention.

The secondary hypothesis is as follows: Compared with the control group, participants (patients with gastric cancer and their spouses) in the experimental group show improvements in the dyadic coping ability measured by the Dyadic Coping Inventory (DCI) after the intervention.

### Theoretical Framework

Manne and Badr [31] believed that it is necessary to not only evaluate the psychological adaptation process of patients in the face of cancer, but also evaluate their spouses. On the basis of summarizing multiple theories, such as the resource theory and social cognition theory, Manne proposed the relationship intimacy model of couple adaptation to cancer [32]. This model divides the factors that affect psychological adaptation into 2 parts: relationship-enhancing behaviors and relationship-compromising behaviors. Relationship-enhancing behaviors, including reciprocal self-disclosure, partner responsiveness, and relationship engagement, have a positive effect on intimacy and psychological adaptation, and intimacy also has a positive effect on psychological adaptation. Relationship-compromising behaviors, including avoidance, criticism, and pressure withdrawal, have a negative effect on intimacy and psychological adaptation. In this model, Manne et al [19] emphasized that reciprocal self-disclosure in relationship-enhancing behaviors is the primary factor affecting the psychological adaptation of patients with cancer and their spouses, and plays a positive role in the face of cancer stressors. This model provides a theory basis for this study to analyze the effect of marital self-disclosure on the fear of cancer recurrence and dyadic coping ability from a binary perspective.

### Methodology and Design

A quasiexperimental study with a nonequivalent (pretest-posttest) control group design will be used to examine the effect of marital self-disclosure on the fear of cancer recurrence and dyadic coping ability among patients with gastric cancer and their spouses. The study will be conducted at 2 tertiary hospitals in Taizhou City, Jiangsu Province, China. Considering the time constraints, sample availability, and prevention of contamination, the research will be conducted in the oncology departments (digestive system) of 2 hospitals. The 2 hospitals will be assigned randomly. A total of 42 patients with gastric cancer undergoing chemotherapy and their spouses will be recruited from each hospital. Eligible patients with gastric cancer undergoing chemotherapy who agree to participate and sign the informed consent form will be included in this research. Participants from Jingjiang People’s Hospital will be assigned to the experimental group, while participants from Taizhou People’s Hospital will be assigned to the control group. Patients with gastric cancer share similar characteristics, such as demographics, treatment, and nursing care plans. The treatment methods refer to the “Guidelines for Diagnosis and Treatment of Gastric Cancer” [32]. The chemotherapy scheme is selected according to the patient’s actual situation, which is predicted for 4 to 6 cycles. The study includes 4 stages of face-to-face interventions. The researchers will take measurements at 3 time points: baseline and 2 and 4 months postintervention.

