### Allocation and Blinding

This study will recruit an equal number of patients with gastric cancer and their spouses. Participants from Jingjiang People’s Hospital will be assigned to the experimental group, while participants from Taizhou People’s Hospital will be assigned to the control group. As the study involves a face-to-face psychological intervention, participants and personnel will be unblinded, but the outcome assessment will be blinded. Participant data will be anonymized using individual participant codes, and the database will not contain participant identifiers (eg, birth dates and case numbers).

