### Data Analysis

Statistical analysis will be conducted using IBM SPSS 21.0 (IBM Corp). The level of statistical significance will be set as α=.05. Descriptive statistics will be used to describe the sociodemographic and psychosocial variables, including percentages, means, and standard deviations. For comparing the baseline characteristics of the 2 groups, the Student *t* test or Mann-Whitney *U* test will be used for quantitative variables and the chi-square test will be used for categorical variables. Two-way repeated-measures ANOVA will be performed to determine the presence of a significant change in the fear of cancer recurrence and DCI in the intervention and control groups in order to analyze the effects of the intervention and compare the control group with the experimental group at baseline and 2 and 4 months postintervention. This analysis will be performed on an intention-to-treat basis. A *P*-value of <.05 will be considered statistically significant for differences between the 2 groups.

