## Discussion

### Marital Self-Disclosure Intervention and Protocol Design

Improvement of the fear of cancer recurrence and dyadic coping ability in patients with gastric cancer is necessary. To date, few psychological interventions effectively manage the fear of cancer recurrence in patients with gastric cancer. This is the first and only intervention with the explicit aim of improving the fear of cancer recurrence in Chinese patients with gastric cancer. The intervention focuses on personal emotional expression, social cognition expression, benefit discovery, and outlook to the future, with a further focus on the fear of cancer recurrence. This study will provide evidence of the effectiveness of the marital self-disclosure protocol for improving the fear of cancer recurrence compared with routine nursing care.

There are several advantages of the marital self-disclosure intervention. First, the study involves a long-term intervention that spans from the participant’s diagnosis of gastric cancer until the end of chemotherapy. In a preview study, among patients with gastric cancer in the first, third, and sixth chemotherapy stages, greater family support was associated with a lower fear of cancer recurrence [7]. Therefore, early and lasting intervention is essential.

Second, the study considers the marital factors related to the fear of cancer recurrence and has developed relevant communication topics in each phase. The husband and wife will be trained in marital self-disclosure, and formal disclosure will be made after both husband and wife have mastered the method of disclosure. Moreover, before each phase, the couple will review the method of disclosure again so that the couple can fully grasp the method of disclosure and return it as a homework exercise, making the research results more credible. Finally, this study combines written and verbal representations to facilitate better participant expression of concerns regarding the fear of cancer recurrence.

Third, the study is based on not only a literature review but also Chinese cultural background, clinical practice, and stakeholder input to design a feasible intervention for Chinese patients with gastric cancer.

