### Limitations

This study has some minor limitations. First, this study involves a long-term intervention, and some participants may not complete the study owing to loss of follow-up or physical deterioration during treatment. Second, missing data may influence the results and must be addressed statistically. To overcome this bias, a 20% attrition rate will be included in the sample size calculation, and an intention-to-treat analysis will be performed during the data analysis. Finally, this study will only include patients during chemotherapy.

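### With one hospital per group, hospital and intervention cannot be separated, and the P value from the planned ANOVA leaves out hospital variance

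*Protocol article*

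**What the plan says.** Methodology and Design labels the study openly: "A quasiexperimental study with a nonequivalent (pretest-posttest) control group design will be used". The same section says "The 2 hospitals will be assigned randomly", and it names the hospital for each group, as does Allocation and Blinding: "Participants from Jingjiang People’s Hospital will be assigned to the experimental group, while participants from Taizhou People’s Hospital will be assigned to the control group". Each group is therefore exactly one hospital. The ground offered for comparing them is "Patients with gastric cancer share similar characteristics, such as demographics, treatment, and nursing care plans"; no data accompany it.

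Under Sample Size, the formula is the one for two independent means, with no allowance for clustering. Under Data Analysis, baseline characteristics are compared by t test or Mann-Whitney test, and "the chi-square test will be used for categorical variables". Nothing is said to follow from those tests. Outcomes go into a two-way repeated-measures ANOVA at a .05 level. No covariate is named, and the text does not say whether the group term or the group-by-time term decides. It speaks both of change and of comparing the groups at each of the three time points. The main hypothesis (Hypotheses) is worded as lower FoP-Q-SF scores after the intervention.

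The Discussion promises that "This study will provide evidence of the effectiveness of the marital self-disclosure protocol for improving the fear of cancer recurrence compared with routine nursing care". Limitations opens with "This study has some minor limitations" and lists attrition, missing data and the restriction to patients on chemotherapy. It does not mention that hospital and group coincide.

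**The concern.** Randomising two units settles which hospital gets the intervention, but it balances neither patients, staff nor ward practice. Whatever differs between the two hospitals also differs between the two groups. The ANOVA error term contains only variation between and within patients, so it treats a hospital difference as if it could arise only from the intervention or from patient-level chance.

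A significant result could then come partly or wholly from case mix, nursing practice or the way fear evolves on each ward. The Introduction and the Conclusion both tie clinical adoption to the intervention being shown effective, so it matters what the P value can and cannot support.

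**Working it through.** **The plan's own figure.** 35 × 1.2 = 42 per group, as stated. The 35 itself cannot be reproduced because no SD is given. Solving the stated formula backwards at 90% power for a 2.88-point difference gives SD = 2.88 × √(35/2) / (1.960 + 1.282) = 3.72. Nothing in the formula allows for hospital variance.

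**Inputs.** From the protocol: one hospital per group, 42 per group (35 before dropout), two-sided 5% test, three time points including baseline. Assumed, because the documents give no values: the hospital ICC (share of total variance lying between hospitals) and, for the simulation, a within-patient correlation of 0.5.

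**Case A: groups compared on level at one time point.** With one hospital per group, the true variance of a group mean (total variance set to 1) is ICC + (1 − ICC)/n. The planned test sees only (1 − ICC)/n. Their ratio is V = 1 + n × ICC/(1 − ICC). The usual design effect, 1 + (n − 1) × ICC, is a simpler and slightly milder approximation. Either way, the actual rejection rate with no intervention effect is 2 × [1 − Φ(1.96/√V)]. With n = 42:

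| Assumed ICC | Design effect 1 + 41 × ICC | Rejection rate | V = 1 + 42 × ICC/(1 − ICC) | Rejection rate | Effective n = 42/design effect |
|---|---|---|---|---|---|
| 0 | 1.00 | 5.0% | 1.00 | 5.0% | 42 |
| 0.01 | 1.41 | 9.9% | 1.42 | 10.1% | 29.8 |
| 0.02 | 1.82 | 14.6% | 1.86 | 15.0% | 23.1 |
| 0.05 | 3.05 | 26.2% | 3.21 | 27.4% | 13.8 |

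At ICC 0.005 the second formula gives 7.5%. More patients do not cure this: effective n per group cannot exceed about 1/ICC, which is 20 at ICC 0.05.

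**Case B: the two terms of the planned ANOVA.** Simulation with 35 per group, three time points, 10,000 runs and no intervention effect:

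| Hospital variance assumed | Group main effect | Group-by-time | Change, baseline to 4 months |
|---|---|---|---|
| None | 5% | 5% | 5% |
| Stable level difference, 2% of variance | 17% | 5% | 5% |
| Stable level difference, 5% | 31% | 5% | 5% |
| Hospital-by-time difference, 1% | 6% | 17% | 13% |
| Hospital-by-time difference, 2% | 9% | 29% | 20% |
| Hospital-by-time difference, 5% | 16% | 52% | 36% |

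A stable difference affects the group main effect and leaves the group-by-time term at its nominal level. A difference in how the two hospitals change over time affects the group-by-time term directly.

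**What the trial can estimate.** With one hospital per group there are zero degrees of freedom between hospitals within a group. Hospital variance cannot be estimated from these data, so no corrected P value can be computed from them.

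**The case against.** The strongest reply is that baseline is one of the levels of the time factor and that Data Analysis speaks of change. If group-by-time decides, a lasting difference between the hospitals cancels, as Case B shows. This stands. A reader might infer that the planned ANOVA necessarily carries baseline differences in fear, stage or education into the result. The documents do not support that, because the deciding term is not named. Nor do they rule it out: the main hypothesis is about scores after the intervention, and the analysis text mentions comparisons at each time point.

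Second, the ICCs are assumed, and at zero hospital variance there is no inflation. This also stands, so the percentages show a range and are not an estimate for this trial.

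Third, a condensed article may leave a covariate list to an analysis plan that is not shown. That is fair, and the missing list alone would be no finding. But no analysis plan can undo one hospital per group, and the statement of similarity, the account of limitations and the promise of evidence are all in the article itself.

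Fourth, the design is declared nonequivalent, with contamination, time and sample availability given as reasons. The label concedes the problem, yet the same section then asserts similarity, and Limitations omits the problem.

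Fifth, the sentence on random assignment reports a procedure and does not claim balance between patients. A reader might infer that it should be struck out; it needs clarifying instead. Finally, baseline-adjusted ANCOVA is not clearly better than an analysis of change when the groups' true baseline means differ, so it should not be imposed as the primary analysis.

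**Conclusion.** The concern holds in this form. Hospital and intervention are the same variable, the planned test uses only patient-to-patient variance, and its P value is too small whenever hospital variance in the contrast tested exceeds zero.

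- For a comparison of levels with 42 per group, the actual rejection rate at a nominal 5% is about 10%, 15% or 26-27% for an assumed ICC of 0.01, 0.02 or 0.05.
- For the group-by-time term, stable differences do no harm. Hospital-by-time variance of 1%, 2% or 5% gives about 17%, 29% or 52% under the simulation's assumptions.

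Two stronger readings go too far. One is that a positive result would be spurious: the documents give no evidence that the two hospitals differ, only no protection if they do. The other is that covariate adjustment would make the P value valid: it can reduce measured imbalance, but it cannot separate hospital from intervention. The analysis and the claims should be corrected before the data are analysed.

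**What to change.** 1. **Data Analysis.** Name the group-by-time contrast, specifically the change from baseline to 4 months in patient FoP-Q-SF, as the deciding test. Adjust it for a short prespecified list of covariates already collected, for example age, gender, education, tumor stage, treatment type and time since diagnosis, whatever the baseline tests show. The covariates should enter as predictors of the change. Give baseline-adjusted ANCOVA as a sensitivity analysis.
2. **Methodology and Design.** Keep the fact of random assignment, but state that only two units were randomised and that this gives no balance between groups. Remove the statement of similar characteristics as a ground for comparability.
3. **Limitations.** List one-hospital-per-group confounding as a major limitation.
4. **Discussion.** Report any difference as an adjusted between-hospital difference whose P value excludes hospital variance, not as proof of effectiveness.

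The cost is wording, a few degrees of freedom and a more cautious claim. No new data are needed: the covariates and baseline scores are already scheduled. Only more hospitals per group, or allocation within hospitals, would separate the two effects. Results reports 97 patients with their spouses recruited by 30 October 2023, against 2 × 42 = 84 planned, so a redesign is probably out of reach for this study.
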